2. platelets (PLT) ≥100×10^9^/L;
3. hemoglobin (Hb) ≥100g/L;

- **Biochemistry:**

1. total bilirubin (TBIL) <1.5×ULN；
2. alanine aminotransferase (ALT) and aspartate aminotransferase (AST) <2.5×ULN; ALT and AST <5×ULN in patients with liver metastases;
3. blood Urea Nitrogen (BUN) and creatinine (Cr) ≤1×ULN or creatinine clearance rate ≥50ml/min (Cockcroft-Gault formula);
4. Women of reproductive age must have already used effective contraception or have negative serum or urine pregnancy test results within 7 days before enrollment and be willing to use an adequate method of contraception during the trial period and 8 weeks after the last drug administration. For men, consent is given to use an appropriate method of contraception or to have been surgically sterilized during the trial period and 8 weeks after the last drug administration;
5. Be willing and able to provide written informed consent for the trial, and comply with all aspects of the protocol.
   1. **Exclusion criteria**

Subjects who meet any of the following criteria are not eligible to enter the study:

1. Small cell lung cancer (including mixed small cell and NSCLC);
2. Symptomatic brain metastases (patients with stable brain metastases who have completed treatment 21 days before enrollment are eligible, but have no symptoms of cerebral hemorrhage confirmed by brain MRI, CT, or venography);
3. Tumor lesion of ≤5 mm from the large blood vessels, or central tumor invading the local large blood vessels, or significant pulmonary cavitary or necrotic tumors by imaging (computed tomography [CT]/ magnetic resonance imaging [MRI]);
4. Patients with hypertension who are being treated with a combination of two or more antihypertensive drugs;
5. Patients with positive T790M mutations from genetic test;
6. Cardiovascular diseases: class II or more of myocardial ischemia or myocardial infarction, arrhythmia due to poorly controlled (including men with corrected QT interval [QTc] ≥450 ms and women with QTc ≥470 ms); patients in New York Heart Association (NYHA) class III-IV cardiac dysfunction, or left ventricular ejection fraction (LVEF) <50% by echocardiography;
7. Patients with a history of interstitial lung disease or concurrent interstitial lung disease;
8. Abnormal coagulation function (INR >1.5 or prothrombin time [PT] >ULN+4 seconds or APTT >1.5 ULN) with a bleeding tendency, or are receiving thrombolytic or anticoagulant therapy;
9. Hemoptysis (2 teaspoons or more per day) before enrollment;

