7. Pregnant or lactating women; A fertile patient who is unwilling or unable to use effective contraception;
8. The investigator identifies other conditions that may affect the proceeding of the clinical study and its outcomes.
   1. **Dropout/removal criteria**
9. Patients who failed to meet the inclusion criteria;
10. Safety evaluation could not be performed without one dose of the drug;
11. Both modern Chinese medicine and immunomodulators approved by SFDA are simultaneously used for the treatment of lung cancer;
12. The dose, method, and course of treatment are not specified according to the study protocol.
    1. **Termination criterion**
13. Withdrawl of informed consent and request to withdraw from the study;
14. Radiographic evidence of disease progression;
15. Pregnancy events occurred during the study;
16. Subjects who were still unable to tolerate toxicity after dose adjustment;
17. Decisions to withdraw from study by the sponsor.
18. Study Drugs
    1. **Overview of drugs**
       1. **Drug information**

Study Drugs are produced by Chia Tai Tianqing Pharmaceutical Group Co., Ltd., and the detailed information is shown in Table 6.1.1.

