In the event of pulmonary symptoms (dyspnea, cough, and fever) gefitinib therapy should be interrupted, and a prompt investigation of these symptoms should occur. If interstitial lung disease is confirmed, gefitinib should be discontinued and appropriate treatment should be conducted.

No dosage adjustment is recommended for patients with different body weights, gender, ethnicity, renal function, or moderate to severe hepatic impairment due to liver metastases.

For patients treated with gefitinib combined with anlotinib who discontinue gefitinib therapy, the decision of proceeding with anlotinib is determined by the investigator.

When AEs occur, dose adjustment of gefitinib and subsequent dosing regimens are determined by the investigator.

- 1. **Management of anlotinib-related AEs**

Management of anlotinib-related AEs will be performed by the investigator based on the actual clinical situation (reference the following management).

1. **Fatigue**

Fatigue is often associated with oncologic treatment, and it is recommended to monitor the onset of severe fatigue by observation and documentation of the patient's fatigue. No dosage adjustment is necessary if grade 1-2 fatigue occurs; aggressive symptomatic treatment should be provided if grade 3-4 fatigue occurs. In absence of jaundice, thrombi, and pregnancy, progesterone drugs (such as megestrol) and multivitamins may be administered to help reduce fatigue and enhance physical performance. In addition, care must always be taken to identify other causes of fatigue such as those secondary to hypothyroidism, depression, anemia, or pain.

1. **Diarrhea**

Diarrhea may impact the digestive function, fluid and electrolyte balance of the patient, and the absorption of medications, early treatment should be performed. Diarrhea usually appears during the first few days of treatment. No dosage adjustment of anlotinib should be performed.

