Hypertension is emerging as one of the most common AEs. The [cardiovascular toxicities](https://www.sciencedirect.com/topics/medicine-and-dentistry/cardiovascular-toxicity) panel of the NCI recommends that patients with hypertension at baseline should be diagnosed before VEGF/VEGFR-inhibitor therapy, and patients should have a sustained blood pressure of <140/90 mmHg during the treatment. Blood pressure (BP) should be performed monitored before administration of the drug and especially in the first 2 weeks of treatment (daily monitoring should be performed), and monitoring must continue throughout treatment. Therefore, for patients with hypertension, the antihypertensive drugs should be administered based on individualized principles before receiving anlotinib to achieve early and favorable BP control (BP of ≤140/90 mmHg). However, prophylactic antihypertensive therapy is not recommended for patients with normal BP. Patients should be adequately informed to contact the investigator immediately for guidance when BP is >140/90 mmHg or when symptoms associated with elevated BP occur (e.g., significant headache, dizziness, visual disturbances, etc.). It has been suggested that antihypertensive drugs should be chosen according to the 2010 Chinese guidelines for the management of hypertension, regarding the risk factors for cardiovascular disease in patients. For patients combined with proteinuria, an angiotensin-converting enzyme inhibitor (ACEI) or an angiotensin receptor blocker (ARB) is recommended. A word of caution in drug selection is required that anlotinib is primarily metabolized by the lung CYP3A4 enzyme. Non-dihydropyridine calcium channel blockers (verapamil and diltiazem) can moderate CYP3A4 inhibition and are not recommended for BP control.

If a grade 3-4 increase in BP occurs, antihypertensive treatment or dose modification of this product should be performed under the guidance of the specialist. Drug discontinuation is recommended if the adverse reaction persists. This product should be permanently discontinued in patients who develop a hypertensive crisis. Recommendations for the prevention and treatment of anlotinib-associated hypertension can be viewed in **Table 7.4.1** hypertension classification criteria (NCI-CTC AE 4.0) and recommendations for prevention and treatment.

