**Table 7.4.1. Classification criteria (NCI-CTC AE 4.0) and recommendations for prevention and treatment**

| Criteria | Definition | Prevention and treatment |
| --- | --- | --- |
| Grade I | SBP 120-139 mmHg, or DBP 80-89 mmHg | Close monitor of BP; Limit sodium intake, and quit smoke and alcohol; Continue to administer anlotinib without dose adjustment. |
| Grade II | SBP 140-159 mmHg, or DBP 90-99 mmHg | Close monitor of BP; Continue to administer anlotinib without dose adjustment; Treatment with antihypertensive drugs, and should not be stopped arbitrarily. |
| Grade III | SBP ≥160 mmHg, or DBP ≥100 mmHg | Suspension of anlotinib; Consider the combination of drugs for hypertension with poor control of monotherapy; Consult a cardiovascular specialist; Close monitor of BP; Continue the drug treatment at a dose reduced by one level with well-controlled blood event |
| Grade IV | Life-threatening (malignant hypertension or  Hypertensive emergencies/persistent neurological deficit) | Immediate and permanent drug discontinuation; Consult a cardiovascular specialist; Aggressive treatment and close monitor of BP and other vital signs |
| Grade V | Death | - |

1. **HFSR**

Patients should avoid mechanical trauma to hands and feet in the treatment, wearing loose-fitting comfortable shoes, softy cotton socks or gloves, and gel inserts, and vigorous exercise which may help limit the reaction; Avoiding direct sunlight on the skin, and using topical emollients or other preparations containing urea or lanolin to protect shin; Avoiding eating hot and spicy food. Treatment of moderate HFSR (if occurs) includes strengthening skin care by mild moisturizer or lubricant to keep the skin clean and moist and avoid secondary infection, pressure, or friction; Topical administration of exfoliating drugs may be administered (such as creams and ointments containing urea, 5% salicylic acid, and corticosteroid lotions), and dissolving the magnesium sulfate in warm water and soaking the affected skin if necessary; Topical antifungals or antibiotics; Appropriately administrating of B vitamins (B1, B6, and riboflavin) and celecoxib. If hyperkeratosis leads to thickened and calloused of foot skin, podiatrists can perform podiatric care to prevent further aggravation and use moisturizing ointment immediately after the pedicure.

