- Antidepressants (amitriptyline, imipramine, clomipramine, dosulepin, and doxepin).
  - 1. **Chinese medicine preparations and immunomodulators with anti-cancer effects**

This protocol prohibits the use the Chinese medicine preparations for the treatment of lung cancer that is approved by CFDA and immunomodulators (such as thymosin, interferon, interleukin-2 zilongjinpian, and fungal polysaccharides).

- 1. **Permitted concomitant medications/treatments**

All treatments that are considered by the investigator to have no effects on study endpoints may be administered, such as unconventional therapies (e.g., herbal or acupuncture) and vitamin/mineral supplements. Bisphosphonates are allowed for subjects with bone metastases during the trial. Palliative radiation therapy in a small area (<5% bone marrow region) will be permitted for subjects with uncontrolled pain of bone metastases after systemic therapy or topical analgesia. Antiviral medication should be administered during enrollment for patients with positive hepatitis B surface antigens during the screening period. Clinical co-morbidities and the emergence of various types of AEs should be treated aggressively. Any combination medications should be recorded in the electronic case report forms (eCRFs) in strict accordance with GCP regulations [[16](#_ENREF_16)].

1. Study Procedures

All patients must read and sign an informed consent form approved by the ethics committee before the initiation of the study. All study procedures are required to be performed according to the time window procedure in the schematic flow diagram (Appendix 2, flow diagrams of anlotinib in combination with gefitinib for NSCLC). Clinical observation and examination time is independent of the duration of drugs, and related examinations (including imaging examinations) are performed at each course of treatment.

- 1. **Screening**

The following procedures must be completed within 4 weeks before study drug initiation (unless specifically indicated).

(1) Sign the informed consent form;

(2) Demographic: Age, sex, occupation, nationality, height, and weight;

(3) Smoking history: Smoking duration, number of cigarettes (light smokers ≤15 cigarettes/day; medium smokers <25 cigarettes/day; heavy smokers ≥25 cigarettes/day)

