(4) Tumor diagnosis: Date of diagnosis for clinically staged, histologic classification (large cell carcinomas and adenocarcinomas), pathological regional (primary and metastatic lesions), TNM classification, and clinical staging.

(5) Gene mutation status (the test results of mutation status must be provided if the patient has been tested).

- EGFR gene mutation status;
- Other gene mutation status (if have).

(6) History of antitumor therapy:

- Tumor surgery: The date and type of previous surgery;
- History of chemotherapy/targeted/immunotherapy (including neoadjuvant and adjuvant therapy): Drug names, dose, administration cycle, onset and duration, best efficacy, and reasons for changing drugs (if due to disease progression, imaging should be recorded; if due to intolerance, AEs and grade of AEs should be recorded).
- Radiotherapy history: radiotherapy time and radiotherapy dose.

(7) The date of the tumor progression or recurrence after the last treatment.

(8) Comorbidities: Such as diabetes, hypertension, or chronic obstructive pulmonary disease.

(9) BP monitoring: BP is measured by the investigator during the screening period; Coffee and tobacco intake are prohibited within 30 minutes before each BP is measured and the measurement is taken in the sitting position with the arm at heart level after at least 10 minutes of quiet sitting, and each BP measurement is taken on the same side.

(10) Imaging examination (CT or MRI): Enhanced CT of the chest, abdomen and enhanced MRI of cranial. For subjects with bone metastases, a whole-body bone scan should be performed; Patients with stable brain metastases should be confirmed without intracranial hemorrhage within 21 days before randomization (written informed consent must be obtained before performing any imagine examination in the trial, except that CT/MRI scan obtained before signing informed consent may be used for screening evaluation if they meet the criteria. The examination must be performed within the first 28 days of the date of the randomization.).

(11) Echocardiography: especially analysis of the values of LVEF (assessments before signing informed consent or within 28 days before randomization if necessary).

(12) Epidemiology: HBs-Ag, Anti-HCV, syphilis, and HIV. HBV DNA test is required if HBs-Ag positive, and HCV RNA test for anti-HCV antibody-positive patients.

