(13) Concomitant medications and therapy: assessments of concomitant medication and concomitant therapy within 28 days before enrollment and during the trial period.

(14) Documentation of AEs: Record AEs from the first dose of the study drug.

The following screening procedures must be completed within 7 days before initiating drug therapy (Blood tests including hemanalysis, blood biochemistry, and coagulation function within 2 weeks before randomization is performed.):

(1) ECOG PS;

(2) Vital signs: Heart rate, respiratory rate, temperature, and BP;

(3) BP monitoring;

(4) Physical examination: Facial features, integumentary system, lymph nodes, eyes, ears, nose, throat, oral, respiratory system, cardiovascular system, abdomen, urinary tract system, musculoskeletal system, nervous system, and spiritual state;

(5) Hemanalysis: Hemoglobin, red blood cell, white blood cells, absolute neutrophil count, lymphocyte count, and platelet count;

(6) Urinalysis: Urine protein, glucose, occult blood (red blood cell and white blood cell), pH, and ketone bodies; If the semi-quantitative method shows the levels of protein ≥2+ (e.g., urine test strip), 24-hour urine analysis are performed and the 24-hour urine analysis of enrolled patients must be < 1g;

(7) Stool tests: occult blood;

(8) Blood biochemistry: TBil, ALT, AST, ALP, r-GT, total protein, Cr, UA, blood glucose, triglyceride, cholesterol, potassium, sodium, chlorine, calcium, urea, and phosphonium;

(9) Coagulation tests: PT, APTT, TT, Fbg, and INR;

(10) ECG: 12-lead ECG. A prolongation of PR-, QTc-, and QT-intervals should be observed and ECG can be performed 3 times consecutively to identify abnormalities (approximately 5-minute interval for each examination and a prolongation of QTc- should be indicated);

(11) Myocardial enzyme profile test: No more myocardial enzyme profile tests except for one test performed within 7 days before enrollment (testing is required if the ECG is abnormal).

(12) Pregnancy test (women of childbearing age);

(13) QoL: The questionnaire should be completed by the subject himself/herself. However, if the subject is unable to read or write, an authorized staff member or guardian could administer it.

The following screening procedures must be performed in screened patients.

1. Subjects who meet eligibility criteria will be randomized by a web-based system and assigned a subject number and treatment groups as well as obtain the dose of the study drug.

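### Section 9.2 requires as few as 6 home BP readings in the first 2 weeks where section 7.4 asks for daily readings (14); secondarily, no eligibility criterion carries a BP value

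*Protocol*

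**What the plan says.** **Monitoring after dosing starts.** The hypertension paragraph of protocol section 7.4 singles out the first 2 weeks of treatment and says BP should be monitored daily in that period. It also tells patients to contact the investigator at once if BP exceeds 140/90 mmHg or if symptoms of raised BP appear. Section 9.2 item 3 has patients record their own BP on a diary card, with a minimum of three readings a week in cycles 1 and 2 and daily readings when BP is abnormal. The investigator also measures BP at each visit. Visits in the first four cycles fall on day 21±3.

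**Status of 7.4.** The section opens with: "Management of anlotinib-related AEs will be performed by the investigator based on the actual clinical situation (reference the following management".

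**Entry.** Section 5.3 item 4, repeated in the synopsis, excludes "Patients with hypertension who are being treated with a combination of two or more antihypertensive drugs". No other criterion in 5.2, 5.3 or the synopsis concerns BP, and none gives a value in mmHg. Section 9.1 provides two pre-dose measurements. Under the 4-week heading ("The following procedures must be completed within 4 weeks before study drug initiation"), "BP is measured by the investigator during the screening period"; BP monitoring appears again under the heading "The following screening procedures must be completed within 7 days before initiating drug therapy". Neither carries a limit. For patients with hypertension, section 7.4 says "the antihypertensive drugs should be administered based on individualized principles before receiving anlotinib to achieve early and favorable BP control (BP of ≤140/90 mmHg". Table 7.4.1 suspends anlotinib at grade III, "SBP ≥160 mmHg, or DBP ≥100 mmHg". The last item of 5.3 allows exclusion where "The investigator identifies other conditions that may affect the proceeding of the clinical study and its outcomes".

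**The concern.** The two sections give different minimum frequencies for the same 2 weeks, and the lower one sits where site staff look for procedures. The difference falls on patients whose readings are still normal, because 9.2 moves to daily readings only after an abnormal one. In a patient without symptoms, the instruction to call when BP exceeds 140/90 mmHg works only if a reading has been taken. Section 7.4 counts hypertension among the most common adverse events. Section 1.5.2.2 puts the peak plasma concentration of the 2-weeks-on, 1-week-off schedule at day 14, the end of this window and before any scheduled clinic reading. A first rise in BP could be seen days late, and how late would vary by site.

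The entry question is separate and weaker. The protocol gives numeric entry limits for QTc, LVEF, INR and urinary protein. BP is measured twice before dosing but has no limit, so sites may differ in what they accept.

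**Working it through.** The plan states no figure to reproduce. The check is a count, plus a reading of the eligibility text.

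**1. Readings in days 1-14**
- Section 7.4: 14 days × 1 = 14.
- Section 9.2 item 3, minimum with normal readings: 2 weeks × 3 = 6.
- Difference: 14 − 6 = 8. The 9.2 minimum is 6/14 = 43% of the daily schedule.

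**2. Longest run of unread days in days 1-14**

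Section 9.2 does not fix the spacing. Take three readings in days 1-7 and three in days 8-14.
- Worst placement: readings on days 1-3 and 12-14 leave days 4-11 unread, which is 8 days.
- Best placement: 14 − 6 = 8 unread days are spread over at most 7 intervals (before, between and after the six readings). At least one interval must then hold 2 unread days, and 2 is attainable.
- Daily reading: 0.

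**3. First scheduled clinic BP after dosing starts**

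The first visit is on day 21±3, so the earliest is 21 − 3 = day 18. The diary readings are the only scheduled ones in days 1-14.

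**4. Cost of alignment over cycles 1-2 (42 days, 6 weeks)**
- Present minimum: 6 × 3 = 18.
- Daily for 2 weeks, then three a week for 4 weeks: 14 + 4 × 3 = 26.
- Difference: 26 − 18 = 8 readings per patient.

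**5. What the phase I data show (Table 3, 12 mg, N = 21)**
- Grade I/II BP increase in the first 2 cycles: 5/21 = 23.8%, exact (Clopper-Pearson) 95% CI 8.2% to 47.2%.
- Grade III in the first 2 cycles: 0/21. Exact upper limit 1 − 0.025^(1/21) = 16.1%.
- Grade III over the whole study: 2/21 = 9.5%.
- Timing within the 2 cycles is not given, so no rate for days 1-14 can be derived.

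**6. Entry criteria**

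| Place | What it fixes for BP |
|---|---|
| 5.2, 5.3, synopsis | No value in mmHg; a count of antihypertensive drugs only |
| 9.1 | Two pre-dose measurement points; no limit |
| 7.4 | Control to 140/90 mmHg or below before anlotinib |
| Table 7.4.1 | Suspension at SBP 160 or DBP 100 mmHg and above |

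Read alone, the listed criteria do not keep out a patient on no drug or one drug whose BP is already at the suspension level. What stands in the way is the 7.4 direction and the investigator's discretion under the last item of 5.3. The documents do not say how many patients would be affected, and no estimate is made.

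**The case against.** **The two frequencies are compatible.** Section 9.2 sets a floor and 7.4 is more specific for the first 2 weeks; a patient who measures daily satisfies both. This stands, so a reader who infers an outright contradiction goes too far. What remains is that compliance with 9.2 does not secure compliance with 7.4. The 8-day gap is the extreme placement that 9.2 permits, not expected conduct.

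**The entry point is a design choice.** Section 7.4 already directs control before anlotinib, BP is measured twice before dosing, and the investigator may refuse entry. This largely stands. A reader might infer that the protocol lets uncontrolled hypertension through without safeguard; read as a whole, it does not. Nor is it safe to dismiss 7.4 as optional. Its opening sentence concerns drug-related adverse events, which pre-existing hypertension is not, and the protocol words plainly operative rules with the same verb (section 7.2 on the maximum length of a dose suspension, for example). What remains is that the target is not an eligibility condition.

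**Appendix 2 is not visible.** Section 9 makes its flow diagram govern procedure timing. If it already schedules daily BP, the practical gap is smaller. This limits certainty about what sites were told.

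**The phase I data show little early harm.** No grade III increase occurred in 21 patients in cycles 1-2, and the 5/21 pools grades I and II, of which grade I needs no antihypertensive drug or dose change under Table 7.4.1. This stands as a limit on weight. With an upper confidence limit of 16.1%, 0/21 does not show that early grade III rises are rare.

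**It may be too late.** Version 1.6 is dated October 29, 2021, and the synopsis estimated last enrolment in June 2021. The document does not say whether enrolment had closed.

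**Conclusion.** The monitoring point holds. In days 1-14, section 9.2 requires 6 readings from a patient with normal BP where 7.4 asks for 14, and no clinic reading is scheduled before day 18. A site working from 9.2 alone under-monitors the period that 7.4 marks out.

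The entry point holds in a narrower form. No criterion gives a BP value, so the pre-dose target of 140/90 mmHg or below is directed by 7.4 but does not decide entry.

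Severity is minor to moderate and concerns patient safety and uniform conduct across sites. The conclusion assumes that Appendix 2 does not already require daily BP in the first 2 weeks and that some sites treat 9.2 as the complete schedule. A reader might also infer harm to patients or an effect on the primary comparison. The documents support neither: they do not time BP rises within the first 2 cycles, and nothing here bears on PFS, power or alpha.

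**What to change.** **Main change.** Reword 9.2 item 3 to require daily BP for the first 2 weeks, then at least three readings a week to the end of cycle 2, and daily readings whenever BP is abnormal. Make the same change in the Appendix 2 schedule if it repeats the 9.2 frequency. The cost is 8 more home readings per patient (26 against 18 over cycles 1-2). It reaches only patients not yet through their first 2 weeks of treatment.

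**Secondary change, only if enrolment is open.** In 5.3, 9.1 and the synopsis, require BP of 140/90 mmHg or below on the screening or pre-dose reading already taken under 9.1. Allow antihypertensive treatment and re-measurement within the 4-week window, and keep the two-drug exclusion. The figure is the protocol's own pre-dose target. A limit set just below the suspension level of 160/100 mmHg would be looser and would close only the suspension-level case. The cost is some delayed or failed screenings, whose number cannot be estimated from the document.
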